## Abstract

**Introduction:**

Individuals with autism spectrum disorder (ASD) who also exhibit severe-to-moderate ranges of intellectual disability (ID) still face many challenges (i.e., less evidence-based trials, less inclusion in school with peers).

**Methods:**

We implemented a novel model called the “Developmental and Sequenced One-to-One Educational Intervention” (DS1-EI) in 5- to 9-year-old children with co-occurring ASD and ID. The treatment protocol was adapted for school implementation by designing it using an educational agenda. The intervention was based on intensity, regular assessments, updating objectives, encouraging spontaneous communication, promoting skills through play with peers, supporting positive behaviors, providing supervision, capitalizing on teachers’ unique skills, and providing developmental and sequenced learning. Developmental learning implies that the focus of training is what is close to the developmental expectations given a child’s development in a specific domain. Sequenced learning means that the teacher changes the learning activities every 10–15 min to maintain the child’s attention in the context of an anticipated time agenda. We selected 11 French institutions in which we implemented the model in small classrooms. Each institution recruited participants per dyads matched by age, sex, and developmental quotient. Patients from each dyad were then randomized to a DS1-EI group or a Treatment as usual (TAU) group for 36 months. The primary variables – the Childhood Autism Rating scale (CARS) and the psychoeducational profile (PEP-3) – will be blindly assessed by independent raters at the 18-month and 36-month follow-up.

**Discussion and baseline description:**

We enrolled 75 participants: 38 were randomized to the DS1-EI and 37 to the TAU groups. At enrollment, we found no significant differences in participants’ characteristics between groups. As expected, exposure to school was the only significant difference [9.4 (±4.1) h/week in the DS1-EI group vs. 3.4 (±4.5) h/week in the TAU group, Student’s *t*-test, *t* = 5.83, *p* < 0.001].

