### Participants and Recruitment

All participants were recruited in outpatient French health care institutions that are specialized in treating children with autism and intellectual handicaps. At the request of the French national health regulatory authority [*Agence nationale de sécurité du médicament et des produits de santé* (ANSM)] and the main sponsor [*Caisse Nationale de Solidarité pour l’Autonomie* (CNSA)], we balanced day care hospitals and special education clinics to have a representative sample of French institutions. In each institution, we obtained a specific commitment to accept the implementation of a DS1-EI school-based program as described below and to recruit the same number of participants to be randomized into a DS1-EI exposed group (called the DS1-EI group) or a treatment as usual (TAU) group who would serve as controls. The commitment also entailed having the required resources from local school authorities to implement the DS1-EI and to have the leading teacher from the classroom be supervised. To avoid bias in the TAU group as a result of the diversity of institutions, we decided to randomize participants by site. Figure 1 summarizes the list of institutions involved in the protocol and the number of patients by site. In total, we enrolled 75 participants.

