**Figure 1 F1:**
[figure not shown]
**Institutions and participants’ enrollment in the DS1-EI trial by site**. HDJ, *Hopital de Jour* (Day care medical center); IME, *Institut Medico-Educatif* (Special education center).

Each parent provided informed written consent before inclusion. The inclusion criteria were a current diagnosis of ASD confirmed by a clinical assessment based on the International Classification of Diseases, 10th edition criteria and the Autism Diagnostic Interview-Revised (ADI-R) (36); an intellectual handicap with financial compensation from local agencies [*Maison Départementale du Handicap* (MDPH)]; being aged between 5 and 9 years; and having a communication developmental age of 24 months and under based on a Vineland assessment or a 3-year speech delay based on a Psycho-Educational Profile, third edition. We did not exclude children with known organic syndromes and/or non-stabilized neuropaediatric (e.g., seizures) or medical (e.g., diabetes mellitus) comorbidities. However, during the medical assessment, we specifically listed comorbidities. The exclusion criteria were limited to parents’ refusal to participate; family’s plans to change institutions in the short term for any reason; and patient’s severe behavioral impairments that would challenge treatment adherence. Of note, this last exclusion criterion was based on local institution staff decision. Before randomization, each site was requested to assess the IQ of the participants based on the Kaufman Assessment Battery for Children second edition (KABC-II) or, failing that, Vineland scores. Based on these results, dyads of participants matched for sex, age, and developmental quotient (DQ) were formed to limit the risk of bias between groups. Randomization before group allocation to TAU or DS1-EI group was performed by drawing lots in each dyad per site so that each site could have a TAU group and a DS1-EI group of three to four participants each. Randomization was performed by the methodological coordinating team at the Salpêtrière Hospital and was independent from local inclusion sites. TAU was defined as all therapeutic interventions given to a specific child. Given the study duration, we did not recommend not to change children’s therapeutic protocol in the TAU group during the study period. The trial duration was defined as 36 months but included 12-, 18-, and 24-month intermediate assessments.

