## Results

### Participants at t0 after Randomization

Table 4 summarizes the participants’ sociodemographic and clinical characteristics at enrollment. As expected, we found no significant differences at enrollment between the DS1-EI and TAU groups, indicating that the randomization by site did not introduce bias. As expected, exposure to school was the only significant difference found between the two groups: 9.4 (±4.1) hours per week in the DS1-EI group vs. 3.4 (±4.5) hours per week in the TAU group, Student’s *t*-test, *t* = 5.83, *p* < 0.001.

**Table 4 T4:** **Sociodemographic and clinical characteristics of the participants after group randomization**.

	DS1-EI group (*N* = 38)	TAU group (*N* = 36)	Test, *p*

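### The abstract reports 75 children randomized (38/37) but Table 4 covers 74 (38/36), and neither split can come solely from lots drawn within complete dyads

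*Protocol article*

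**What the plan says.** The counts appear in three places.

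- Abstract, Discussion and baseline description: 75 enrolled, of whom "38 were randomized to the DS1-EI and 37 to the TAU groups".
- Methods, Participants and Recruitment: "In total, we enrolled 75 participants". No split by arm is given there; it refers to Figure 1 for the numbers by site.
- Results, Table 4: the caption reads "Sociodemographic and clinical characteristics of the participants after group randomization", and the column headers are 38 for DS1-EI and 36 for TAU.

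The allocation method is in Participants and Recruitment. Children were matched on sex, age and developmental quotient, and "Randomization before group allocation to TAU or DS1-EI group was performed by drawing lots in each dyad per site". The draw was made by a coordinating team independent of the sites. Each institution had committed to "recruit the same number of participants to be randomized into a DS1-EI exposed group" or a TAU group, and each site was to have three or four children per arm.

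The text available reports no withdrawal or exclusion between the draw and Table 4, no unpaired child, and no rule for allocating one.

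**The concern.** The article gives two different sizes for the randomized TAU arm, 37 and 36. The size of the randomized set is a figure the rest of the trial depends on. It should be the denominator for the 18- and 36-month comparisons, and it is the starting point for the between-group comparison of drop-outs announced in Statistical Analysis. The Results section also relies on Table 4 to conclude that randomizing by site introduced no bias, and that conclusion should rest on every child who was randomized.

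The second difficulty is the imbalance itself. One lot per matched pair puts one child in each arm, so the arms must be equal. Unequal arms mean that the described method does not, on its own, account for every child in the reported counts.

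**Working it through.** **Inputs.** Abstract: 38 DS1-EI, 37 TAU. Participants and Recruitment: 75 in total. Table 4: headers 38 and 36, plus the categorical rows. Participants and Recruitment: allocation by lot within dyads, per site.

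**1. The article's own total.** 38 + 37 = 75. The abstract agrees with itself and with the Methods.

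**2. Table 4 total.** 38 + 36 = 74. The difference is 75 − 74 = 1, all of it in TAU (37 − 36 = 1).

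**3. Is 36 a header misprint?** The row counts can be summed. Row labels in the sociodemographic block are shifted by a line in the text as read, but the male/female counts are identifiable and the sums do not depend on the label.

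| Row | DS1-EI | TAU |
|---|---|---|
| Sex | 32 + 6 = 38 | 30 + 6 = 36 |
| Known medical condition | 34 + 4 = 38 | 27 + 9 = 36 |
| Disability level by KABC | 27 + 3 = 30 | 26 + 3 = 29 |

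The printed TAU percentages fit 36: 30/36 = 83% and 9/36 = 25%, against 30/37 = 81% and 9/37 = 24%. (One other percentage in the medical-condition row is garbled, but the counts are legible.)

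**4. Is it item-level missing data?** The KABC row covers only 30 and 29 children under unchanged headers, so the table keeps a child in N when a test result is absent. The unaccounted child is absent even from the sex row, and sex was a matching variable. A missing score is therefore not a natural explanation.

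**5. Can the test statistics settle it?** They cannot. Recomputing the CARS t-test from the tabulated means and SDs gives t = 0.671, p = 0.504 with 36 TAU children and t = 0.676, p = 0.501 with 37. The table prints 0.67 and 0.504. That is slightly closer to 36 but not decisive, because the inputs are rounded and other rows (CGAS, for example: 0.418 or 0.421 against a printed 0.38) are not reproduced by either number.

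**6. Dyads.** With k complete dyads and one child of each per arm, the arms are k and k and the total is 2k.

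- 38/37: at most 37 complete dyads, so at least 38 − 37 = 1 DS1-EI child has no counted partner. The total of 75 is odd and cannot equal 2k.
- 38/36: at most 36 complete dyads, so at least 38 − 36 = 2 DS1-EI children have no counted partner, although 74 is even.

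Totals that would fit are, for example, 37 + 37 = 74 or 38 + 38 = 76.

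**7. Size.** 1/75 = 1.3% of all children; 1/37 = 2.7% of TAU. At the article's planning effect size of 0.6, with a two-sided 5% level, power ≈ Φ(0.6 × √[n₁n₂/(n₁+n₂)] − 1.96). This gives 73.8% for 38/37 and 73.2% for 38/36, a difference of 0.6 percentage points.

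**The case against.** The count mismatch is not open to dispute, but what it implies is. A reader might infer that a randomized control child was dropped after allocation, so that the 36-month comparison starts on a subset and a TAU loss is hidden from the drop-out comparison. The documents do not support that. No exclusion or withdrawal is reported. The figure of 37 could itself be the slip. Table 4 is descriptive and is not said to define the analysis population, and nothing in Statistical Analysis removes this child from the mixed models or the drop-out comparison. Figure 1, which gives the numbers by site, could not be seen and may bear on the cause. This objection stands.

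A reader might also infer that some child was allocated outside the described randomization. That goes too far as well. A leftover child may have been allocated by a simple central lot, or a partner may be missing from the reported count. Site groups of three or four would tolerate a four-against-three site, although this sits awkwardly with the commitment to equal numbers per arm.

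It can further be said that handling of a leftover child is detail for the full protocol, and that one child in 75 changes nothing. The first is fair as far as the rule's absence goes, but the article itself prints counts that its stated method cannot produce alone. The second is right about numerical effect. Neither removes the contradiction, since the article chose to report both totals.

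**Conclusion.** The article contradicts itself on the size of the randomized set: 75 (38/37) in the abstract, against 74 (38/36) in the table captioned as covering the children after randomization. Two TAU rows summing to 36 make a header misprint or a missing test score an unlikely explanation. One TAU child is unaccounted for in the text available. Separately, neither split can arise solely from lots within complete dyads, so at least one child was unpaired or a partner is missing from the count.

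The effect is small, at 1 of 75 children. Nothing here shows a biased estimate, a material loss of power, or an improper exclusion. The conclusion rests on the printed counts being read correctly and on a dyad meaning one child to each arm. The cause is not known from the documents, and which total is right cannot be decided from them. It is still worth correcting, because the randomized denominator should be settled before the 18- and 36-month outcomes are analyzed.

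**What to change.** Check the allocation list held by the coordinating team and state one randomized set, by arm. Use it as the denominator for Table 4, for the mixed-model population and for the drop-out comparison.

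- If 37 TAU children were randomized, include the 37th in Table 4 and the analysis, or, if that child left after the draw, count the child as a TAU drop-out at time zero and say so.
- If 36 is right, correct the abstract and the total in Participants and Recruitment, or explain there that one enrolled child was not randomized.

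In either case, add a sentence on how many children had no dyad partner and how they were allocated.

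The cost is a check of an existing list and a few corrected figures. If the 37th child has to be added to Table 4, it also depends on that child's baseline data being on file, which the documents do not say.

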**Ethics and dissemination:**

The protocol was authorized by the competent national regulatory authority (*Agence nationale de sécurité du médicament et des produits de santé*) and approved by the local Ethics Committee (*Comité de Protection des Personnes*) at the University Hospital Saint-Antoine (May 7, 2013). The findings will be disseminated through peer-reviewed journals and national and international conferences.

**Trial registration numbers:**

ANSM130282B-31 (April 16 2013) and ACTRN12616000592448 (May 6 2016).

## Background

Autism spectrum disorder (ASD) is characterized by the presence of atypical social communicative interaction and behaviors. The role of some genetic factors in ASD is known. However, there is a growing body of neurobiological research that indicates the presence of complex gene–environment interactions. Despite these findings, there is no approved biological treatment for this disorder and the first-line treatments pertain to psychosocial domains (1). Typically, ASD is diagnosed by means of a behavioral analysis during the 3- to 5-year-old age range; once diagnosed, the treatment is primarily delivered through behavioral interventions following different models. In essence, these models try to promote cognitive, communication, and behavioral skills that are considered essential to improve social skills in the long run (2, 3).

Several global interventions for core deficits in ASD have been proposed and assessed within clinical trials. The Treatment and Education of Autistic and Communication Handicapped Children (TEACCH) program uses many technical interventions to meet the individual needs of people with autism. The work program is tailored to some seminal aspects of ASD. First, it is centered on the individual. Individual needs are assessed through a comprehensive assessment of several developmental dimensions while taking into account emerging capacities. Second, it requires an understanding of autism, the adoption of appropriate adaptations and a broadly based intervention strategy (e.g., structured teaching, visual understanding, object manipulation, social communication skills) that builds on existing skills and interests. Third, the environment is organized to help children and adults understand and remember what to do (e.g., visual agendas, making expectations clear, and explicit, visual materials, structured architecture). The focus is on positive strategies to support behavioral and teaching strategies (4, 5).

Applied Behavioral Analysis (ABA) is a one-to-one intensive method that uses reinforcement of adaptative and acquired skills (6). The first structured attempts by Lovaas (7) were criticized (difficulties in generalization of learned behaviors; mechanical responses; lack of spontaneity) despite their encouraging first results. These criticisms led to the development of Pivotal Response Training [PRT], a more naturalistic behavioral treatment that has good documented effectiveness (8). PRT is a home-based intervention that includes parents in the routines. The method is based on choosing “pivotal” skills as the target of the treatment; following the child’s choice of activities and games; reinforcing not only the correct answer expected by the professional but also all (meaning complete or incomplete) forms of attempts to respond; alternating between acquisition and maintenance; and using intrinsic reinforcers.

The Early Start Denver Model (ESDM) is an early and intensive intervention approach for young children. The interventions are based on the following: (i) a curriculum that evaluates the child’s development across different developmental domains; (ii) specific procedures for learning and incorporating ABA principles, such as PRT; (iii) sessions focusing on interactions with children, interpersonal exchanges, and shared commitment with materials and activities of daily living; (iv) a positive affect, adults being responsive and sensitive to child cues; (v) verbal and non-verbal communication cues; (vi) proximal developmental windows, meaning that the focus of training is what is close to the developmental expectations given a child’s development in the according domain; and (vii) parents’ involvement. This program is implemented in small groups or individually at a specialized center or at home (3, 9).

The Developmental, Individual Differences, and Relationship-based (DIR) method is built on three axes: (i) the level of functional and emotional development reached by the child; (ii) the individual differences in information processing and motor planning; and (iii) the types of interactions that the child establishes with his/her partners (10). Floor Time is the core of the DIR method. It consists of sequences of guided play (15–20 min) that are repeated several times by parents throughout the day and are supervised by an expert. The DIR principles that should always be respected are to follow the child’s lead and support his/her initiative; to focus on joint attention; to close circles of communication; to create semi-structured problem solving; to contrast repetitiveness with playful obstruction; to support visual attention; and to work on imitation (10, 11).

In an attempt to capture the common components among these models and what could be learned from evidence-based studies, Narzisi and colleagues (12) delineated the following principles: the first group regards timing: (1) starting as early as possible; (2) minimizing the gap between diagnosis and treatment; (3) being intensive (not less than 3–4 h of treatment per day); the second group is based on viewing parents as partners and involving family; the third group gathers principles related to treatment program: (1) providing regular assessments, supervision and updating the goals of treatment; (2) encouraging spontaneous communication; (3) promoting skills through play with peers; (4) finalizing the acquisition of new skills and their generalization and maintenance in natural contexts; and (5) supporting positive behaviors rather than tackling challenging behaviors.

### Why Should We Implement a School-Based Intervention?

Despite the encouraging results presented earlier, most of those programs (a notable exception being TEACCH) do not target school-aged children and are not proposed to occur in a school setting. This is unfortunate because schools are a favorable location for autism interventions (13). Additionally, many children with ASD do not receive a sufficient amount of treatment (14), even in countries with free access to health care (15). Because children with ASD benefit from being with other peers at school, the gap between education research and education practice (16) may be a missed opportunity to offer more support to these children. Additionally, larger doses of treatment could be offered in school contexts, especially when interventions are administered 1:1 (17). Several agencies have recommended conducting interventions in school-based settings (18, 19). Two objectives should be combined: school-based core deficit interventions and school-based social communication practice (20). There are already several studies that have shown that school-based interventions are able to reach larger numbers of children with ASD. This may improve challenges with generalization by using learned skills regarding communication in a natural environment, such as in the classroom (21, 22). Additionally, the preschool context seems to offer opportunities to develop communication skills (23, 24), and by offering opportunities to enter into play groups, teachers can supply reinforcements of the non-verbal ASD child requests (25).

However, there are very few school-based social communication interventions, and in many cases, teachers at school do their best without guided specific interventions for ASD children in the classroom. Consequently, there is a lack of response from teachers to the communicative acts produced by children with ASD (26). General educational teachers provide infrequent verbal prompting with ASD children (27), and they more frequently engage in functional play than symbolic play (28). They also lack supervision (20). Thus, there is a paradox between the need for appropriate intensive interventions for ASD and what is proposed in most school settings. For example, Mudford and colleagues (29) showed that the implementation of an evidence-based ABA program in preschoolers was not complete: 93% of the participants were not provided the dose of treatment (40 h/week). Additionally, from an efficiency perspective, although several programs support the concept of tailoring interventions to the child’s needs and skills, to our knowledge, no one has questioned whether programs could be adapted according to teaching local skills.

### Why Should We Study Children with ASD and Intellectual Disability?

As expressed in the dimensional approach of the new classifications in the DSM-5 (30), intellectual disability (ID) is a frequent challenge and comorbidity in ASD. According to studies, ID co-occurs in 50 to 75% of ASD cases (31). Risk factors of comorbid ID in ASD are gender (despite the high number of males with ASD, the male/female ratio decreases in ASD comorbid with ID) and the existence of seizures or of a neurodevelopmental or genetic syndrome (32, 33). The co-occurrence of ID also appears to be a prognostic factor for long-term outcomes of ASD (12, 34) and a risk factor of the incidence of challenging behaviors that provoke severe morbidity in some cases (35). To date, very few models have specifically addressed ASD comorbid with ID, in particular when ID is in the severe-to-moderate range. Therefore, the need to focus on this understudied population is warranted. Here, we wonder whether or not children with comorbid ASD and severe ID may be receptive to a pedagogical content? For such children over 5 years, could an adapted and one-to-one cognitive program in school be a road to improve non-verbal and verbal communication and to promote social skills?

